## Abstract

**Introduction:**

Individuals who access at-risk mental state (ARMS) services often have unusual sensory experiences and levels of distress that lead them to seek help. The Managing Unusual Sensory Experiences (MUSE) treatment is a brief symptom targeted intervention that draws on psychological explanations to help account for unusual experiences. Practitioners use formulation and behavioural experiments to support individuals to make sense of their experiences and enhance coping strategies. The primary objective of this feasibility trial is to resolve key uncertainties before a definitive trial and inform parameters of a future fully powered trial.

**Methods and analysis:**

88 participants aged 14–35 accepted into ARMS services, experiencing hallucinations/unusual sensory experiences which are considered by the patient to be a key target problem will be recruited from UK National Health Service (NHS) sites and randomised using 1:1 allocation (stratified by site, gender, and age) to either 6–8 sessions of MUSE or time-matched treatment as usual. Participants and therapists will be unblinded, research assessors are blinded. Blinded assessment will occur at baseline, 12 weeks and 20 weeks postrandomisation. Data will be reported in line with Consolidated Standards of Reporting Trials. Primary trial outcomes are feasibility outcomes, primary participant outcomes are functioning and hallucinations. Additional analysis will investigate potential psychological mechanisms and secondary mental well-being outcomes. Trial progression criteria follows signal of efficacy and uses an analytical framework with a traffic-light system to determine viability of a future trial. Subsequent analysis of the NHS England Mental Health Services Data Set 3 years postrandomisation will assess long-term transition to psychosis.

**Ethics and dissemination:**

This trial has received Research Ethics Committee approval (Newcastle North Tyneside 1 REC; 23/NE/0032). Participants provide written informed consent; young people provide assent with parental consent. Dissemination will be to ARMS Services, participants, public and patient forums, peer-reviewed publications and conferences.

**Trial registration number:**

ISRCTN58558617.

STRENGTHS AND LIMITATIONS OF THIS STUDYThis is a feasibility randomised controlled trial, results will address key uncertainties to inform a future large-scale trial, including sample size and design decisions.The Managing Unusual Sensory Experiences intervention toolkit, the trial design and participant facing materials have been developed with substantial input from people with lived experience.This study is distinctive in exploring potential causal cognitive mechanisms in an at-risk mental state population who have unusual sensory experiences.There is no gold standard treatment to compare the intervention to, so controlled time-matched treatment as usual is selected as the comparator.The follow-up period is short (20 weeks postrandomisation), therefore, longer-term participant impacts will not be fully assessed; however, long-term transition to psychosis will be examined via the Mental Health Services Data Set.

## Introduction

At-risk mental state (ARMS) describes presentations that indicate a potential prodromal stage of psychosis, or risk of psychosis, with around 25% of ARMS individuals converting to psychosis within 36 months.^1^ The importance of working with these individuals to target possible unhelpful beliefs in development, reduce distress, support healthy functioning and potentially to prevent the development of full psychosis is widely advocated.^2 3^

The presence of unusual sensory experiences, such as hearing voices and seeing visions (hallucinations), may not in themselves indicate mental ill health as there may be common underlying psychological mechanisms or a continuum of experience from benign, everyday experiences to more severe hallucinations that require treatment.^4^ However, increased frequency and intensity of hallucinations, alongside distress and a decline in functioning, are linked to transition to psychosis and are threshold criteria in scales recommended in ARMS services.^5 6^ Intervening to reduce the distress of unusual sensory experiences and offer explanations of the possible mechanisms behind these experiences may be key in preventing transition to psychosis.^3 7^

Current UK National Institute for Health and Care (NICE) guidelines recommend that people meeting ARMS criteria should be referred for specialist assessment and offered cognitive–behavioural therapy (CBT) to reduce the risk of developing psychosis.^8–10^ While approaches involving CBT and CBT with supportive therapy show promise in ARMS, the evidence for CBT improving functioning and mental state, or reducing progression to psychosis, is inconclusive.^11–13^ No specific psychological intervention has been identified as having superior effectiveness in its treatment; there is no gold-standard treatment.^11 14 15^ ARMS services, therefore, need to further assess interventions that indicate potential benefit. Robust clinical trials are needed to determine benefits vs risk profiles, accessibility and cost-effectiveness.^11 13 16^

Treatment development would be improved if they addressed key causal mechanisms leading to distressing experiences, and adapted treatment to the needs of different age groups.^17 18^ Taking a staged or stepped approach to psychological intervention is good practice, usually with CBT and needs-based interventions prior to pharmacology.^8 18 19^ There is scope for research into briefer approaches implemented prior to CBT in ARMS services, and emerging evidence from early intervention in psychosis (EIP) research that inclusion of briefer targeted evidence-based interventions prior to CBT may result in a reduction of need for more in-depth CBT, as people better understand their experiences and have less need for interventions.^20^

Through extensive multidisciplinary research into voice hearing, clinically embedded research with patients who are indicating at risk state for psychosis, and studies of first episode psychosis, we have developed a targeted, computer/web-based guided self-help psychoeducation toolkit for distressing hallucinations (managing unusual sensory experiences, MUSE).^7 21^ MUSE endeavours to provide scientific and normalising explanations that may provide acceptable and helpful understandings of an individual’s unusual sensory experiences and help to prevent more delusional explanations from developing. MUSE has been trialled with an ARMS patient group in a non-randomised study^21^ and shown to be acceptable with good participant satisfaction with the therapy. We intend to assess MUSE through a series of trials to determine patient benefit and possible impact on progression to psychosis in patients at high risk. We will also seek to learn more about whether change relates to target mechanisms underlying hallucination subtypes.^22^ This could be important for further refinement of treatment.

### Objectives

#### Primary objective

To conduct an ISRCTN-registered feasibility randomised controlled trial to resolve key feasibility uncertainties and inform the parameters of a future trial, to investigate the preliminary effect of MUSE+treatment as usual (TAU) versus time-matched supportive psychotherapy TAU on general functioning (assessed using the Social and Occupational Functional Assessment Scale (SOFAS),^23^ and mental state related to frequency and distress of unusual sensory experiences and false beliefs (assessed using the Psychotic Symptom Rating Scales (PSYRATS)^24^ total score, and sub-scales Hallucinations and Attribution^25^) in ARMS patients post therapy and at 5 month postrandomisation follow-up.

#### Secondary objectives

To explore additional treatment effects on unusual sensory experiences, anxiety, depression and quality of life, and whether there are indications of other factors (sleep disturbance and trauma) influencing treatment effects.

To test feasibility of collecting measures of psychological mechanisms, including psychological and personal (phenotypical) factors implicated in the clinical course of hallucinations. To analyse which psychological mechanisms are influenced by the treatment and contribute to its clinical effect and inform a future investigation of whether any efficacy of MUSE is through impact on these mechanisms.

To collect routine data for a future records investigation testing feasibility of tracking transition to psychosis through medical databases (hospital records/Mental Health Services Data Set (MHSDS)), to examine which features of MUSE (presenting, treatment response and mechanistic) are most relevant to psychosis prevention.

## Methods and analysis

### Trial design and flow chart

This is a feasibility trial employing a prospective randomised, open-label, observer blinded, endpoint design assessing a targeted, computer/web based guided self-help psychoeducation toolkit for distressing hallucinations (MUSE)+TAU (6–8 sessions) compared with a TAU time-matched control (also referred to as supportive psychotherapy) (6–8 sessions) offered by a multidisciplinary team which includes needs based emotional support, psychoeducation and stress management, aiming to reduce distress from hallucinations and improve functioning, in people with an ARMS for psychosis in UK secondary care mental health services.

The trial has received National Health Service (NHS) Research Ethics positive opinion (23/NE/0032) and Health Research Authority Approvals and is registered with the ISRCTN registry (ISRCTN58558617, registered 9 May 2023). Two substantial amendments followed first approval and were obtained prior to first participant consent: Amendment 1 notably added in an unvalidated Preferences Questionnaire for therapeutic intervention, and changed an anxiety self-report questionnaire over to use the State-Trait Anxiety Inventory-Short Form (STAI-Short Form).^26–28^ Amendment 2 replaced a longer dissociative experiences questionnaire for the eight-item Brief Dissociative Experiences Scale (DES-B)-Modified.^29 30^

The trial has an independent trial steering committee (TSC) and Lived Experience Advisory Panel (LEAP) facilitated by a coapplicant for the study with lived experience of psychosis.

### Participants

Recruitment will be via NHS secondary care mental health clinical teams providing ARMS services. Patients who potentially meet the eligibility criteria for the trial, and their parent/guardian where appropriate if under 18 years, will be informed of the study by a member of their clinical team. Participants will be checked for eligibility prior to informed consent via discussion with referring teams and in the participant–researcher discussion prior to giving informed consent. Participant information sheets will be provided at least 3 days prior to the informed consent meeting. Written informed consent in adherence to principles of Good Clinical Practice will be obtained prior to participation. For participants aged 14 and 15 years old, parent/guardian informed consent with child assent will be taken; this option of assent with parent/guardian consent will also be made available to participants aged 16 and 17 years old due to their potential vulnerability and the governing UK law which classes a minor as someone who is under 18 years old. Verbal consent form will be used for participants with literacy challenges. Interpreters and translated consent forms will be available for participants who do not speak English. Participants will be given £15 honorarium for each assessment time point.

### Trial eligibility criteria

#### Inclusion criteria

In contact with an ARMS service or accepted on an ARMS pathway by EIP services.Aged 14–35.Hallucinations/unusual sensory experiences scoring at least three on the Perceptual Abnormalities Subscale of the Comprehensive Assessment of ARMS (CAARMS).^6^
Hallucinations considered by the patient to be a key target problem.Judged to have been clinically stable for the preceding 2 weeks.

#### Exclusion criteria

intellectual disability or severe cognitive dysfunction affecting ability to engage with research materials.lacking capacity to give informed consent.

### Randomisation and blinding

Eligible participants who have completed baseline assessments will be randomised and subsequent assessments will be scheduled from the point of randomisation. An independent web-based randomisation service (sealedenvelope.com) will be used for the trial. Randomisation will be in the ratio 1:1 to the two groups: MUSE+TAU (intervention) or TAU time-matched control (supportive psychotherapy+TAU (control). Randomisation will be stratified by site, gender (M/F/other) and age (14–17 years/18–35 years inclusive). Randomisation allocation will be independent and dynamically generated using a randomised modified minimisation method^31^ to assure allocation concealment along with preservation of allocation ratio. Randomisation allocation is made known to the CI and site PIs, the trial coordinator(s) and the trial therapists only at the point of randomisation, by email.

Research assessors for the trial will be blind to the allocation throughout the trial. Clinicians, therapists and participants will be unblind. Trial statisticians will be partially blind; In the first instance, for the analyses and reporting of main outcomes of the trial the Statisticians will be fully blind. However, for secondary sensitivity analysis such as impact of number of MUSE sessions on effect size) and the mechanisms investigations, the statisticians will be required to view which participants received MUSE treatment.

### Assessments

Assessors blinded to trial allocation will complete participant assessments at baseline, 12 weeks postrandomisation, and 20 weeks postrandomisation (see table 1). Sociodemographic information will be collected from the participant at baseline only (CSRI questions 1–3.5 as amended for the trial^32^).

**Table 1 T1:** Trial assessments and key participant procedures schedule

Assessments/procedures	Participant identification	Enrolment and baseline	Randomisation	Intervention weeks 1–12	12 weeks postrandomisation (±10 days)	20 weeks postrandomisation (±10 days)
Recruitment and eligibility discussions	X					
Informed consent		X				
CSRI Sociodemographic Q1-3.5		X				
Randomisation			X			
MUSE and TAU/TAU intervention				[figure not shown]		
Blinded assessments						
MUSE ARMS primary outcome measures: SOFAS and PSYRATS		X			X	X
CSRI service use Q4.1–4.4		X				
CSRI Q4.5 criminal justice services and Q5 medication		X			X	X
MUSE ARMS secondary outcome measures: CAARMS-PA, PHQ-9, GAD-7, ReQoL-20, ISI, ITQ/ITQ-CA, MMHQ		X			X	X
Subtype measures and cognitive tasks (1–2 subtypes selected per participant)		X			X	X
Treatment preference		X				
Unblinded assessments						
CSRI service use at follow-up Q4.1–4.4					X	X
Transition to psychosis data					X	X
Adverse event data					X	X
Therapeutic alliance STTS-R					X	
Participants interviews (withdrawals subsample)						
Participants interviews (MUSE completers sub-sample)						
Participants interviews (TAU subsample)						
Therapists interviews (subsample)						

ARMS, at-risk mental state; CAARMS-PA, Comprehensive Assessment of At-Risk Mental States subscale of Perceptual Abnormalities; CSRI, Client Services Receipt Inventory; GAD-7, Generalised Anxiety Disorder Assessment;; ISI, Insomnia Severity Index; ITQ/ITQ-CA, International Trauma Questionnaire/International Trauma Questionnaire - Child and Adolescent Version; MMHQ, Multi-Modal Hallucinations Scale; MUSE, managing unusual sensory experiences; PHQ-9, Patient Health Questionnaire; PSYRATS, Psychotic Symptom Rating Scales; ReQoL-20, Recovering Quality of Life; SOFAS, Social and Occupational Functional Assessment Scale; STTS-R, Satisfaction with Therapy and Therapist Scale-Revised.

### Primary indicators of outcome

The primary outcome measures are: (1) Feasibility outcomes, including qualitative interviews; (2) General functioning assessed using the SOFAS,^23^ a clinician/clinical researcher rated single-item scale; (3) Target problem hallucinations assessed using the PSYRATS^24^ (hallucination total) clinician/clinical researcher rated interview, and; (4) Distress and Attribution dimensions of target problem assessed using the PSYRATS.^25^

### Secondary assessments

Additional assessments will be the clinician/clinical researcher administered semi-structured interview CAARMS subscale of Perceptual Abnormalities^6^ to elicit further detail about the nature of unusual experiences. Self-reported measures will rate depression symptom severity using the Patient Health Questionnaire (PHQ-9^33^), anxiety using the Generalised Anxiety Disorder Assessment (GAD-7^34^), quality of life using the Recovering Quality of Life measure (ReQoL-20^35^), sleep difficulties using the Insomnia Severity Index (ISI^36^) and trauma using the International Trauma Questionnaire/Child and Adolescent Version (ITQ/ITQ-CA^37 38^). An unvalidated measure, the Multi-Modal Hallucinations Questionnaire (MMHQ) will be used to assess cross-modal sensory experiences.

### Service use

Assessment of potential contamination of the MUSE intervention within the TAU condition, of other psychological therapies use within the treatment arms, and the need for additional interventions beyond the treatment phase will be captured using the CSRI^32^ (as amended for the trial) at baseline, 12 weeks and 20 weeks follow-up. CSRI service use data at 12 weeks and 20 weeks will be collected from medical notes by the unblinded researcher to preserve blinding of research assessors.

### Mechanisms assessment

To assess further information on mechanisms, subtype measures and cognitive tasks will be selected per participant for 1–2 hallucination subtypes: (1) Inner speech, using the Varieties Of Inner Speech Questionnaire,^39^ and computerised cognitive tasks Auditory Signal Detection Task and Auditory Reality Monitoring Source Memory Task^40 41^; (2) Memory, using the DES-B-Modified^29 30^ and computerised cognitive task Inhibition of Currently Irrelevant Memories^42^; (3) Hypervigilance, using the STAI-Short Form,^26–28^ and computerised cognitive Jumbled Speech Task,^43 44^ and (4) Visual, using the visual section of the Plymouth Sensory Imagery Questionnaire,^45^ and computerised cognitive tasks Visual Signal Detection,^46^ Visual Reality Monitoring^47^ and Face Pareidolia Task.^46^ Researchers receive training on subtype selection. Selections are monitored and evaluated against MUSE therapist subtype selections to assess selection reliability and potential training needs.

### Acceptability assessment

To assess therapy preference, satisfaction and acceptability of the intervention, participants will be asked about treatment preferences at baseline using a study specific preferences questionnaire (see online supplemental material 1), and treatment satisfaction postintervention using the Satisfaction with Therapy and Therapist Scale-Revised (STTS-R).^48 49^ Qualitative interviews with participants and trial therapists will further explore experience of MUSE, TAU and trial procedures.

10.1136/bmjopen-2023-076101.supp1Supplementary data

### Long-term outcomes

Long-term transition to psychosis outcomes will be collected 3 years post baseline via the NHS England MHSDS.

### Data management

Interview/clinical assessments data will be scored following the visit and entered onto Qualtrics by the researcher. Source data will be retained in the site file. Self-report data will be entered directly onto Qualtrics during visits using participant ID and visit as markers. Unblinded data on service use will be entered onto Qualtrics at the visit time points. Qualtrics outputs and computerised cognitive task data will be downloaded and date stamped at regular intervals to allow data audit. The full data set will be transferred in its anonymous form to the stats team on completion of data lock at the end of the trial. Trial monitoring at sites will occur across the life cycle of the trial and will follow the sponsor approved data monitoring plan.

### Intervention: MUSE+TAU

The MUSE intervention is a novel targeted, computer/web-based guided self-help psychoeducation toolkit and psychological treatment manual for managing distressing hallucinations in mental health, developed and owned jointly by Durham University and CNTW. Patients work with experienced therapists, under expert supervision, who use the MUSE package within therapy sessions to develop a formulation explaining the development of hallucinations and foster new skills and strategies for their management. The MUSE treatment is divided into the following modules: What are Voices?; How the Mind Works; Assessment (of participant subtype); Inner Speech; Memory and Trauma; Hypervigilance; and Sleep (see Dudley *et al*
50 for details).

Six to eight 1-hour sessions will be offered weekly by experienced therapists who are clinical psychologists or psychological therapists. Therapists will be accredited or working towards accreditation by the British Association of Behavioural and Cognitive Psychotherapists, employed by the ARMS service and have experience of MUSE, receiving clinical supervision and fortnightly MUSE supervision. MUSE is loaded onto therapists smart tablet/NHS laptop (not reliant on Wi-Fi) and is available to patients via the CNTW website between sessions. No personal data are recorded or stored on MUSE toolkit.

Session by session measures will be used as part of the MUSE package to enable therapists to monitor any variations in hallucination frequency and distress that may have a bearing on the selection of module used or revisited during the treatment session.

Therapists will be asked to complete adherence checklists for each session contained within a per-participant MUSE Therapist Pack (see online supplemental material 2). With consent, each session will be audiorecorded to enable independent review by the site Principal Investigator or delegated clinical lead of a random 10% sample to ensure fidelity to protocol within and across sites.

10.1136/bmjopen-2023-076101.supp2Supplementary data

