### Control condition: time-matched control+TAU

To control for risk of bias from an undefined comparative treatment, and potential bias from dose effects, a time-matched TAU is included.^11 51^ In order to match the comparative brief intervention to usual practice within ARMS services, components of care were identified in an engagement meeting with ARMS service leads. These common core components could be described as supportive psychotherapy or ongoing care (needs-based emotional support, psychoeducation, normalisation and stress management) and were outlined as the interventions used by therapists as part of their normal clinical toolkit, alongside routine multidisciplinary care from the team. Patients work with different therapists who are ARMS clinicians and are not trained in MUSE. These clinicians will receive supervision on their practice through the routine supervision arrangements of their service and will record the interventions used within a per-participant TAU Therapist Pack (see online supplemental material 3). We will investigate how frequently and consistently these supportive psychotherapy interventions are offered to inform whether these interventions could act as a comparator intervention in future trials. This arm will be time-matched controlled, however, variation across services precluded using this comparator being defined as a controlled intervention. Number of sessions received in this group will be recorded for analysis.

10.1136/bmjopen-2023-076101.supp3Supplementary data

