### Sample size

As this is a feasibility trial there is no formal sample size calculation, interim analyses or stopping rule. The trial aims to recruit 88 participants with 70 participants completing the study (allowing for 20% attrition) to be able to robustly calculate the sample size for a definitive trial.^53^

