### Criteria for proceeding to a future trial

The signal of efficacy is dependent on the primary outcome data (SOFAS, PSYRATS Total, PSYRATS distress, PSYRATS attribution) and follows: (1) Go: primary outcome data suggest the intervention may show an effect indicating clinical value warranting further investigation; (2) Refine: primary outcome data indicate no measure of effect, but one or more secondary outcomes indicates an effect and (3) Stop: no effect across any outcomes.

The trial progression criteria will follow signal of efficacy and cover domains of research delivery, therapy engagement and fidelity, and safety. The criteria were influenced by LEAP and TSC input and sign-off. Trial progression criteria use an analytical framework with a traffic-light system (see online supplemental table 1). Progression will depend on: (1) All Green outcomes: no/minor revisions prior to next development of the trial or (2) One or more Amber (but not Red) outcomes: If feasible, substantial alterations to the trial protocol, assessments or intervention, supported by the qualitative work-stream and discussed with the Trial Management Group and TSC prior to the next development of the trial or; (3) If one or more Red outcomes result then the trial is unlikely to progress at that site or very substantial amendments are needed. The mechanism measures and tasks will also be reviewed for sensitivity to change and reliability to inform the next development of the trial.

10.1136/bmjopen-2023-076101.supp7Supplementary data

Decisions regarding any changes will consider the ADePT decision-making process to address potential problems with intervention, clinical setting, or trial design that may be relevant in either a trial setting or real world context. We will use qualitative data to contextualise our progression criteria, to ensure that the participant feedback informs our understanding of our research delivery and signal of efficacy.

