### Adverse events

Serious adverse events (SAEs) are defined as: results in death; is life-threatening; requires hospitalisation or prolongation of existing hospitalisation; results in persistent or significant disability or incapacity; results in congenital anomaly or birth defect; or is otherwise considered medically significant by the investigator. Any SAEs shall be assessed immediately for trial relatedness and expectedness and reported to the Sponsor. Any related and unexpected SAEs and any Urgent Safety Measures (defined as: early withdrawal of participant(s) due to safety concerns about the intervention or assessments, or; changes to procedures due to concerns about staff or participant safety) shall be reported immediately to the Sponsor and Research Ethics Committee in accordance with Health Research Authority governance regulations (see: https://www.hra.nhs.uk/approvals-amendments/managing-your-approval/safety-reporting/) and sponsor standard operating procedures.

Adverse events will be recorded for all participants where the event relates to mental state, with focus on clinically significant: (A) increases in distress and/or psychosis; (B) increased harm to self/harm to others; (C) increased suicidal ideation/attempts; (D) increased use of drugs/alcohol; (E) emergency room visits for mental health concerns and(F) access to crises services.

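### Adverse events are collected unblinded, and structured session-by-session symptom monitoring is described only for MUSE, so by-arm counts of worsening distress or psychosis are open to differential detection

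*Protocol article*

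**What the plan says.** All references are to the protocol article.

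- **Scope of adverse events** (Adverse events): "Adverse events will be recorded for all participants where the event relates to mental state, with focus on clinically significant: (A) increases in distress and/or". The item ends by naming psychosis. Five further categories follow: harm to self or others, suicidality, substance use, emergency visits and crisis-service access. The section gives no threshold or common source for category (A).
- **Who collects them** (Assessments, Table 1): the row "Adverse event data" stands in the block of unblinded assessments, at 12 and 20 weeks, on the same schedule for both arms. Randomisation and blinding states that clinicians, therapists and participants all know the allocation.
- **MUSE arm** (Intervention: MUSE+TAU): "Session by session measures will be used as part of the MUSE package to enable therapists to monitor any variations in hallucination frequency and distress". The stated reason is to guide the choice of module. Therapists also have fortnightly MUSE supervision, and sessions are audiorecorded with consent.
- **Control arm** (Control condition): the clinicians are not trained in MUSE, and their therapist pack is described as a record of the interventions used. On oversight: "These clinicians will receive supervision on their practice through the routine supervision arrangements of their service".
- **Use of the data** (Criteria for proceeding to a future trial): the progression criteria "cover domains of research delivery, therapy engagement and fidelity, and safety".
- **Assessor-rated measures** (Assessments; Primary indicators of outcome): blinded assessors rate SOFAS and PSYRATS in both arms at baseline, 12 and 20 weeks.

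**The concern.** Category (A) is a judgement. An event enters the record only if someone notices a worsening and considers it clinically significant. Two features of the design bear unequally on that step. MUSE therapists have a structured reading of hallucination frequency and distress at each session, and nothing comparable is described for control clinicians. The recording itself is also not blinded.

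More noticing in MUSE would raise its count. Judgement that knows the allocation could push the count either way. Safety is one of the progression domains, and the article says that a Red outcome means progression is unlikely at that site or that very substantial amendments are needed. With about 44 people per arm, a handful of events recorded in one arm and missed in the other could change how safety is read.

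**Working it through.** **The plan's own figure.** Sample size states: "The trial aims to recruit 88 participants with 70 participants completing the study (allowing for 20% attrition"). 70 / (1 − 0.20) = 87.5, rounded up to 88, so the figure reproduces. "Randomisation will be in the ratio 1:1 to the two groups" gives 88 / 2 = 44 per arm. Expected non-completers are 88 − 70 = 18, or about 9 per arm if losses are equal.

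**Passages side by side.**

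| Feature | MUSE | Control |
|---|---|---|
| Contact | 6–8 sessions | 6–8 sessions, time-matched |
| Usual-care monitoring by the team | yes | yes |
| Session-level symptom measure | described | none described (therapist pack not shown) |
| Supervision | clinical plus fortnightly MUSE | routine service arrangements |
| Adverse event schedule | 12 and 20 weeks, unblinded | 12 and 20 weeks, unblinded |
| PSYRATS and SOFAS by blinded assessors | yes | yes |

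Time-matching equalises contact, not symptom measurement. Team monitoring goes to both arms, so the MUSE measures come on top of it.

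**Illustration of size.** The article gives no event rate and no detection rate, so both are assumptions here. Let the true category (A) risk be p in both arms, and let detection be d(M) in MUSE and d(C) in control.

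- Recorded risk = p × d
- Apparent risk ratio = d(M) / d(C)
- Excess recorded MUSE cases = 44 × p × (d(M) − d(C))
- 95% half-width of the risk difference = 1.96 × √[a(1−a)/44 + b(1−b)/44], where a and b are the recorded risks

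With p = 0.20 and d(M) = 0.90:

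| d(C) | Recorded risk, MUSE v control | Ratio | Excess cases | Half-width |
|---|---|---|---|---|
| 0.80 | 0.18 v 0.16 | 1.13 | 0.9 | 0.157 |
| 0.70 | 0.18 v 0.14 | 1.29 | 1.8 | 0.153 |
| 0.50 | 0.18 v 0.10 | 1.80 | 3.5 | 0.144 |

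Over p from 0.10 to 0.40 and d(C) from 0.50 to 0.80, the excess runs from 44 × 0.10 × 0.10 = 0.4 to 44 × 0.40 × 0.40 = 7.0 cases. The spurious risk difference runs from 1 to 16 percentage points, against half-widths of about 11 to 20 points.

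The direction is also assumed. If allocation-aware judgement led to under-recording in MUSE, with detection of 0.70 against 0.90 in control, the ratio would be 0.70 / 0.90 = 0.78. With equal detection it is 1.00.

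**The case against.** The strongest reply is that nothing in the article connects the session measures to the adverse event record. Their stated purpose is module selection, adverse events are recorded for everyone on one schedule, contact is time-matched, and both arms receive regular monitoring from the team. Audiorecordings are reviewed only as a random 10% sample, for fidelity. The control therapist pack and the traffic-light table are in supplements not shown, and no between-arm test of adverse events is stated. Unblinded collection also has a plausible reason: the Service use section assigns follow-up service-use data to an unblinded researcher so that assessors stay blind, and the same logic may apply here. Finally, assessor-rated PSYRATS and SOFAS are already modelled as change from baseline by arm.

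Most of this stands. A reader might infer that the safety comparison is biased against MUSE, or that it cannot be interpreted. The document does not support either claim, because the step from session score to adverse event entry is never described. Nor can one say that a Red would follow, since it is unknown whether category (A) counts or any arm contrast enter the safety criterion. Emergency visits and crisis-service access also depend much less on session measures.

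Three things remain. The session measures are described as part of a package that control clinicians are not trained to use, which is more than silence about the control arm. A therapist who has seen a rising distress score has information that a colleague without the measure lacks, whatever the measure was meant for. And modelling mean change does not show how many individuals got worse, since average improvement can sit alongside a deteriorating minority.

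**Conclusion.** The point holds as a risk, not as a demonstrated bias. Category (A) counts by arm are open to differential detection, because recording is unblinded and structured session-level monitoring of hallucination frequency and distress is described for one arm only. The session measures taken alone would point to over-counting in MUSE, but unblinded judgement can act in either direction, so the net direction cannot be derived from the document.

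Nor can the size. The ratios of 1.13 to 1.80 are one assumed detection rate divided by another. They show only that plausible inequality could amount to between less than one case and seven cases in 44. That is within sampling uncertainty for a between-arm difference, yet enough to colour a descriptive safety reading.

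It might seem natural to replace category (A) with visit scores and to take MUSE-detected harms out of the comparison. That goes too far. It would lose events between visits and people who leave the study (about 9 per arm expected), and it would favour MUSE by setting aside harms seen only there. PHQ-9 should not serve as the check, because it is self-reported by participants who know their allocation. PSYRATS and SOFAS are rated by blinded assessors, although PSYRATS still draws on an interview with an unblinded participant. They are the best symmetric measures already in the schedule, and they are not free of all bias.

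**What to change.** 1. Leave all adverse event and SAE recording and reporting as it is.
2. Add a by-arm table to the safety report and to the safety progression review. It should give the number of participants with a pre-set deterioration from baseline on assessor-rated PSYRATS and SOFAS at 12 and at 20 weeks, with the number missing per arm at each visit. The trial team sets the definition before any data by arm are seen. Show the table beside the adverse event counts, not in place of them.
3. In the adverse event listing, flag events known only through MUSE session measures or MUSE supervision. Keep them in, so that the counts can be read with and without them.

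If the two sources agree, the category (A) counts gain credibility. If MUSE shows more recorded events but no more deterioration on assessor ratings, unequal detection becomes one explanation to weigh, alongside transient worsening and missing visits.

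The cost is one table from data already collected and one extra field in the listing. The limitation is that visit-based scores miss transient worsening and dropouts, which is why they supplement the counts.
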